## Abstract

Spastic paresis, a frequent consequence of stroke, is characterized by both neurological and muscular alterations, leading to decreased muscle strength, increased passive muscle stiffness, and subsequently, diminished functional capacity. Although conventional rehabilitation programs are effective in enhancing muscle strength, they often fail to yield clinically significant improvements in functional capacities. Eccentric Training (ET) has shown promise in addressing the shortened muscle fascicle lengths and joint contractures commonly observed in stroke survivors. Despite the prevalence of contractures and rigidity in this population, the effects of ET on the structural and mechanical properties of muscles remain underexplored. This study aims to investigate the impact of ET on gait speed in sub-acute stroke patients compared to conventional therapy. Additionally, we aim to explore the effects of ET on the mechanical properties, structural characteristics, and neuromuscular parameters of the plantar flexors. A randomized controlled trial will be conducted, adhering to CONSORT guidelines, with participants assigned to either a Conventional Therapy Group or an Eccentric Training Group. Assessments will be conducted at baseline, and after ET intervention, encompassing clinical, biomechanical, and functional evaluations. This study seeks to provide empirical evidence on the efficacy of ET in improving motor outcomes in sub-acute stroke patients, thereby informing more effective rehabilitation strategies.

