Recently, an increasing amount of recent research is focusing on muscle strengthening, particularly eccentric training (ET) (24). ET, a traditional method used to boost muscle strength in athletes, involves muscle contraction during the lengthening of the musculotendinous complex (25). Compared to other training modalities at the same force exertion level, eccentric exercise requires less muscle activity (26). Therefore, this approach could be particularly effective for addressing muscle fascicle shortening and stiffness observed in stroke survivors, due to the increased mechanical load involved during active lengthening (14). This increased load is hypothesized to lead to more significant gains in muscle strength and volume and may also reduce hyperactivity in affected muscles (24). In this context, ET has been demonstrated to enhance muscle strength, reduce spasticity, and improve functional performance and quality of life in chronic stroke survivors following 4 to 6 weeks of intervention (27, 28). As a result, ET offers a myriad of benefits that may be relevant for individuals with neurological conditions (27). However, to our knowledge, no study has investigated the effects of ET on the structural and mechanical properties of the PF, nor on their implications for improving functional capacities. This is particularly relevant given the high prevalence of stiffness in post-stroke patients, which is associated with alterations in the structural and mechanical properties of the muscle-tendon complex, consequently limiting functional capacities (29). These issues are challenging to address in neurorehabilitation, where conventional therapy often fail to produce clinically significant results (30, 31). In fact, conventional therapy, which generally involves stretching exercises, concentric training, and repetitive movements to relearn skills such as balance and locomotion, does not appear to significantly improve the patient’s functional walking abilities beyond 0.04 m/s (32).

The objectives of this study are: (i) investigating the effects of eccentric training on the structural and mechanical properties of PF in stroke survivors compared to conventional therapy, and (ii) analyzing the relationships between changes in structural and mechanical parameters of PF and improvements in walking speed and maximal range of motion.

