#### Functional parameters

2.6.1

First, gait speed (m/s) will be measured through the 10-meter walking test. Secondly, the maximal range of motion (ROM), defined as the extent of stretch that the participant can comfortably endure during the stretching maneuver, will be measured using the BIODEX isokinetic device (Biodex 4 Medical Systems, Inc., Shirley, NY, United States). Participants will be positioned prone on the isokinetic machine and instructed to achieve complete relaxation. To minimize the involvement of unrecorded muscles, the ankle will be securely fixed in a relaxed position on the isokinetic dynamometer. Starting from the neutral position (0°), the ankle joint will be passively mobilized from plantar to dorsiflexion at a slow angular velocity (2°/s). Participants will be encouraged to maintain a state of relaxation and halt ankle rotation when they will perceive a tolerable maximum stretch. Then, the ROM (°) will be recorded for each participant.

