### Statistical methods

2.8

Statistical analysis will be conducted using Prism 7.0 software (GraphPad Software, Inc., San Diego, United States). The normality of data distribution will be assessed using Kolmogorov–Smirnov tests. If the data follows a normal distribution, the paired t-test (for comparing the same group before and after intervention) and independent t-test (for comparing the control and experimental groups) will be employed. If the data does not follow a normal distribution, the Wilcoxon signed-rank test (paired samples) and the Mann–Whitney U test (independent samples) will be applied. Relationships between different parameters and their variations will be evaluated using Pearson’s correlation analysis. Data will be presented by their means and standard deviations. The chosen significance threshold will be set at *p* < 0.05 for all results.

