## Limitations

4

One notable limitation of this study is the heterogeneity within the stroke patient population. Even though participants are in the sub-acute phase, the variability in individual recovery trajectories, severity of stroke, and pre-existing health conditions could lead to significant differences in response to the interventions. This heterogeneity may influence the outcomes and interpretations, making it challenging to draw definitive conclusions that are broadly applicable to all sub-acute stroke patients. We aim to increase the sample size to minimize the effects of data heterogeneity and interpretation bias. Furthermore, this study will focus on penniform muscles. It has been suggested that SWV measurements with small deviations from the fiber direction, as determined by the probe-fascicle angle, may be potentially inaccurate (56). However, previous study on the GM have shown relatively reproducible stiffness measurements (57).

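### The Abstract and the stated objectives rank gait speed and muscle properties in opposite order, and one 0.05 threshold for all results leaves no comparison singled out as confirmatory

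*Protocol article*

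**What the plan says.** The Abstract leads with a between-arm question on walking: "This study aims to investigate the impact of ET on gait speed in sub-acute stroke patients compared to conventional therapy". It then adds the muscle outcomes in a softer register: "Additionally, we aim to explore the effects of ET on the mechanical properties, structural characteristics, and neuromuscular parameters of the plantar flexors".

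The Introduction ends with the formal objectives. Objective (i) is "investigating the effects of eccentric training on the structural and mechanical properties of PF in stroke survivors compared to conventional therapy". Objective (ii) is "analyzing the relationships between changes in structural and mechanical parameters of PF and improvements in walking speed and maximal range of motion". Comparing gait speed between arms is not an objective in this list.

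The opening of the Discussion follows the Introduction's ranking. It presents the trial as a comparison of structure and mechanics, and brings in gait speed as something expected to be associated with stiffness. Its hypothesis about the difference between the two interventions names no outcome.

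Section 2.6 describes functional, biomechanical, structural and neuromuscular outcomes and calls none of them primary. Section 2.8 plans paired tests within each arm, an "independent t-test (for comparing the control and experimental groups) will be employed" (or its rank-based counterpart), and correlations. It closes with "The chosen significance threshold will be set at *p* < 0.05 for all results".

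**The concern.** The two statements of aim differ in rank, and rank is what identifies the primary outcome. Under the Abstract the trial succeeds or fails on gait speed. Under the listed objectives it succeeds or fails on a family of muscle measurements, and gait speed matters only through its correlation with them.

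A decision rule could have settled this, but the stated one gives every result the same standing. A report could then follow the plan as written and still choose its headline after the data are seen. A null walking result could be reported as success on stiffness under objective (i), and a null stiffness result as success on walking under the Abstract. The error rate attached to such a claim is not 5%.

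**Working it through.** The article states no outcome count and no overall error rate, so there is no figure of its own to reproduce. The only stated design figure is the 0.05 threshold. Sidedness is not given, so two-sided is assumed.

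**Count of between-arm tests** (one comparison per outcome at the final assessment, Jf):

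- Section 2.6.1: gait speed and maximal range of motion = 2
- Section 2.6.2, passive stiffness: 3 muscles × 3 ankle positions = 9
- Section 2.6.2, active stiffness: 3 muscles × 4 levels (30, 50 and 70% of MVC, and MVC itself) = 12
- Section 2.6.3: fascicle length, thickness, pennation angle = 3
- Section 2.6.4: absolute peak force, relative peak force, early and late RFD = 4
- Section 2.6.4: EMG at MVC in 4 muscles = 4

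Total: 2 + 9 + 12 + 3 + 4 + 4 = 34.

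**How far the count moves with the reading:**

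- Without stiffness at MVC: 34 − 3 = 31.
- Without EMG at MVC: 34 − 4 = 30. Section 2.7 normalises all EMG to the MVC value; applied to the MVC recording itself, this gives 100% by construction.
- Without both: 27.
- With EMG during the passive tests in 4 muscles: 34 + 4 = 38.
- Section 2.7 also refers to different regions within each muscle but gives no number, so regions are not counted.

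**Chance of at least one false positive, independent tests:** 1 − 0.95^k.

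- k = 27: 0.750
- k = 31: 0.796
- k = 34: 0.825
- k = 38: 0.858

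At k = 34 the expected number of false positives is 34 × 0.05 = 1.7.

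**Correlated tests.** The outcomes will be correlated, and the article gives no correlations. As an assumption, 34 test statistics were simulated as standard normal variables with a common correlation (200,000 draws, two-sided 0.05). The last column counts only results favouring eccentric training, for which a single test would have an error of 0.025.

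| Common correlation | At least one significant, either direction | At least one favouring eccentric training |
|---|---|---|
| 0 | 0.83 | 0.58 |
| 0.3 | 0.70 | 0.38 |
| 0.5 | 0.53 | 0.27 |
| 0.7 | 0.35 | 0.18 |
| 0.9 | 0.18 | 0.09 |

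**Further tests under the same threshold.** One between-arm and two within-arm tests per outcome give 3 × 34 = 102. Objective (ii) relates 2 functional measures to 9 + 12 + 3 = 24 muscle measures, which is 2 × 24 = 48 correlations. These are not in the error rates above.

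**The case against.** The strongest reply is that section 2.8 gives only a nominal threshold. It nowhere says that significance on any one outcome counts as success, and a hierarchy or adjustment is commonly left to an analysis plan or full protocol, neither of which is shown. The Abstract's wording for the muscle outcomes is already close to an exploratory label, and section 2.6.1 opens with gait speed: "First, gait speed (m/s) will be measured through the 10-meter walking test".

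Part of this stands. A reader might infer that the plan adopts a rule of winning on any outcome. It does not state one, and the absence of a hierarchy from a condensed article is not in itself the fault. What remains is in the text: two rankings of the aim that cannot both hold, and a single threshold expressly extended to all results. Listing gait speed first in the methods is an order of description and does not designate it as primary.

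It can also be said that 34 is a derived count and that 0.83 requires independence. Both are true. Many outcomes are the same shear modulus in the same leg at neighbouring angles or torques, and relative peak force is absolute peak force divided by body mass, so correlation is likely. A reader might conclude from the independent figure that a positive trial is nearly certain even if eccentric training does nothing. The correlated and favourable-only figures do not support that.

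Finally, the Discussion is not wholly on the side of the Introduction. It gives a paragraph to walking performance and offers sub-acute timing as this trial's response to mixed earlier walking results. That shows that walking matters to the trial, but it does not restore gait speed as a between-arm objective.

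**Conclusion.** The point holds. The Abstract conflicts with the Introduction and the opening of the Discussion on which question is primary, and section 2.8 does not resolve it. If the significance of any outcome can be headlined, the false-positive chance over 34 between-arm tests is about 0.35 to 0.83 for common correlations from 0.7 down to 0. Counting only results favouring eccentric training, it is about 0.58 with independence and 0.27 at a correlation of 0.5. These figures are well above 5% but fall short of near certainty.

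They rest on a count that could be 27 to 38, on two-sided testing, and on an assumed equal correlation among outcomes. The contradiction itself depends on none of these. An unseen full protocol or analysis plan may name a primary outcome; the article would still need to agree with it.

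The remark in the Limitations about increasing the sample size might be read as part of the same problem. It is a separate matter: it does not bear on which aim is primary, and a condensed article may leave the target to the full protocol.

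**What to change.** Reconcile the Abstract, the objectives in the Introduction and the opening of the Discussion to one pre-specified primary comparison, with outcome and time point. If the Abstract reflects the plan, this is the between-arm difference in gait speed at Jf. If the objectives reflect the plan, one muscle outcome must be named and the Abstract changed to match. The choice should follow what was pre-specified, which the article alone does not show.

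In section 2.8, replace the blanket sentence: confine the confirmatory two-sided 0.05 test to the primary comparison, and label all other outcomes, the within-arm tests and the correlations as secondary or exploratory, reported as estimates with 95% confidence intervals. If any of them are to support claims, state a multiplicity procedure. A fixed-sequence test with one key mechanical secondary is one acceptable option among several. Keeping all 34 confirmatory under Bonferroni would require 0.05 / 34 = 0.00147 per test.

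The cost is wording in four places. No measurement, visit or treatment changes. The downside is that fewer results can be called significant.

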## Introduction

1

Stroke, as the leading cause of adult disability, presents a substantial challenge for affected individuals (1). Among the primary impairments following a stroke is the weakening of the lower limb muscles (2), impacting over 90% of stroke patients (3). While some recovery of lower limb function is observed, it often falls short of enabling independent and comfortable outdoor ambulation in daily life (4). Consequently, approximately half of stroke survivors are unable to resume their professional activities, and roughly two-thirds experience chronic disability (5).

One of the primary neuromotor consequences of a stroke is spastic paresis, known as the most common motor disorder following a cerebral injury (6). Generally, the spastic paresis syndrome is associated with both neurological and muscular disorders (7). Neurological issues manifest immediately after a stroke, leading to a quantitative reduction in the recruitment of motor units in agonist muscles (8). This has been explained by a failure of central voluntary control activation and changes in the structure and properties of spinal motoneurons (9). These alterations lead to a decrease in muscle contraction efficiency, resulting in a diminished capacity to generate voluntary force (10). In addition to the previously mentioned neurological alterations, a stroke also triggers muscular changes (11). These alterations, referred to as spastic myopathy, result from a combination of two factors: the underuse of the paretic limb and immobilization in a shortened position (12). Spastic myopathy induces multiple adaptations in the mechanical and structural properties of the paretic muscle (2, 13). In this context, studies have demonstrated a loss of fascicular length and thickness of plantar flexors (PF) (14) and a decrease in pennation angle of the gastrocnemius medialis (GM) in stroke survivors (15). Regarding mechanical adaptation, stroke injury leads to muscle contracture, which is defined as an increased muscle stiffness during passive mobilization of the ankle joint (14, 16).

Several studies have investigated many rehabilitation programs for stroke survivors and found that a regular musculotendinous stretching is effective in short-term spasticity inhibition and in preventing long-term hypo-extensibility and muscle contracture; muscle strengthening is recommended as soon as voluntary motor control allows for it; relearning grasping (17), balance (18), and locomotion involves the repetition of motor tasks (19). Otherwise, many studies have concluded, with a high level of evidence, the effectiveness of botulinum toxin in reducing spasticity (20). However, motor improvement remains mild to moderate (21). These mixed results concerning motor function improvement are likely related to the evaluation methods of movement-limiting factors and muscle hyperactivity, which are lengthy, intrusive, and destructive (3, 13). They also do not focus on reducing the effects of spastic myopathy, which is still not well-understood in management (22, 23). Therefore, it is both justified and necessary to question the post-stroke rehabilitation and readaptation methodologies.

Recently, an increasing amount of recent research is focusing on muscle strengthening, particularly eccentric training (ET) (24). ET, a traditional method used to boost muscle strength in athletes, involves muscle contraction during the lengthening of the musculotendinous complex (25). Compared to other training modalities at the same force exertion level, eccentric exercise requires less muscle activity (26). Therefore, this approach could be particularly effective for addressing muscle fascicle shortening and stiffness observed in stroke survivors, due to the increased mechanical load involved during active lengthening (14). This increased load is hypothesized to lead to more significant gains in muscle strength and volume and may also reduce hyperactivity in affected muscles (24). In this context, ET has been demonstrated to enhance muscle strength, reduce spasticity, and improve functional performance and quality of life in chronic stroke survivors following 4 to 6 weeks of intervention (27, 28). As a result, ET offers a myriad of benefits that may be relevant for individuals with neurological conditions (27). However, to our knowledge, no study has investigated the effects of ET on the structural and mechanical properties of the PF, nor on their implications for improving functional capacities. This is particularly relevant given the high prevalence of stiffness in post-stroke patients, which is associated with alterations in the structural and mechanical properties of the muscle-tendon complex, consequently limiting functional capacities (29). These issues are challenging to address in neurorehabilitation, where conventional therapy often fail to produce clinically significant results (30, 31). In fact, conventional therapy, which generally involves stretching exercises, concentric training, and repetitive movements to relearn skills such as balance and locomotion, does not appear to significantly improve the patient’s functional walking abilities beyond 0.04 m/s (32).

The objectives of this study are: (i) investigating the effects of eccentric training on the structural and mechanical properties of PF in stroke survivors compared to conventional therapy, and (ii) analyzing the relationships between changes in structural and mechanical parameters of PF and improvements in walking speed and maximal range of motion.

## Materials and methods

2

### Ethical approval and trial registration

2.1

The study protocol, patient information letter, and informed consent form received Institutional Ethics Committee approval (CPP 2022–038 = 000117). The study is registered in the ClinicalTrials.gov database (ID = NCT06140381). The procedures will be conducted according to the principles expressed in the Declaration of Helsinki. Written consent to participate in the protocol will be signed directly by the patient.

### Study design

2.2

This study will be conducted in strict adherence to the Consolidated Standards of Reporting Trials (CONSORT) guidelines, and will employ a single-blinded, controlled, randomized design, wherein participants will be randomly assigned to one of two groups: the conventional therapy group (CTG) or the Eccentric training group (ETG). Both groups will undergo a series of assessments at: Ji (initial assessment) and Jf (final assessment) as illustrated in Figure 1. The study will begin with a recruitment phase, followed by a screening phase. Subsequently, there will be a 4-week period allocated for experimental testing before the intervention, and an additional 4 weeks for experimental testing after the intervention. The experimental testing will include clinical health assessments, biomechanical assessments, neuromuscular evaluations, and functional assessments.

**Figure 1 fig1:**
[figure not shown]
Study design.

### Randomization

2.3

The random assignment of participants to their respective groups will take place on the day they will be included in the study and will be supervised by the investigator. The randomization list will be created by an independent statistician from the clinical research unit. For the randomization process, a computer-generated list will be generated using the Clinical Trial Randomization Tool. This list will then be uploaded into an online case report form. Each study participant will be assigned a unique allocation study number in a sequential format (TMP00X). The rigorous blinding will be maintained until the database will be finalized. A blinded assessor will conduct three visits: one before, one in the middle, and one after the interventions, while unblinded kinesiologists, who provide treatment and exercise sessions, will not be involved in the assessment sessions. All required information stipulated by the study protocol will be entered diligently into the Electronic Data Capture system in real-time as it will be acquired.

### Recruitment

2.4

Participants will be recruited from the clinic of Parc de Belleville in Paris between the 1st of January 2024 to 31st May 2024. Recruitment will be accomplished by disseminating study participation offers in clinical centers, and subsequently, the medical staff will compile a list of volunteers to the experimenter. To participate in this study, subjects will be invited for an admission consultation (Pre-inclusion) (J0) with the principal investigator. Before this consultation, the investigator will need to ensure that the patient meets the study’s inclusion and exclusion criteria.

